### **Literature Review**

A large number of studies have explored the utility of text reminders for the provision and utilization of health services. A recent review of mobile telephone text messaging (short message service, SMS) identified 60 studies assessing the impact of mobile phone based reminders on health service utilization [6]. Most studies in the current literature focus on adherence to medication, such as malaria [4], HIV [7] and management of chronic illness, such as diabetes and hypertension [8]. Systematic reviews for both HIV and long-term self-managed care suggest moderate size, but generally statistically significant increases in adherence to treatment [6, 7]. Mobile text messages have also been increasingly used to increase attendance of health care appointments: the latest systematic review suggests that text reminders can increase attendance of scheduled appointments significantly and are likely a cost-effective tool in this setting [9]. Evidence is much more limited on preventive behavior; a 2012 Cochrane review identified only one moderate quality study focusing on vitamin C intake, and a second high quality study focusing on smoking cessation [10]. In a more recent review focusing directly on vaccination, six randomized controlled trials using text reminders were identified; all six of these trials were conducted in high income settings, and focused mostly on older populations [11]. To our knowledge, there is no study that has looked at the effectiveness of mobile text reminders for increasing early vaccination coverage in a low income setting.

In terms of alternative interventions to improve vaccination coverage in low income settings, regular immunization outreach has been identified to be most effective in improving full immunization coverage, especially if combined with household incentives (the last Cochrane review finds a risk ratio of 6.66 for full vaccination coverage, even though this evidence was classified as low-certainty) [12].

Given this background, we believe that the proposed interventions have high potential to improve early vaccination coverage, and hope that the proposed pilot investigation will provide first evidence in support of this hypothesis.

## Study Design Overview

The study will be designed as an open label cluster-randomized controlled study with three arms: a control arm, a reminder-only arm, and a reward arm. During the intervention phase community volunteers will be appointed to register all births in 10 randomly selected treatment communities. In each active treatment arm, an estimated 100 women across five villages will be enrolled in a proactive program. In intervention group A, participating women will receive reminders about vaccinations recommended at birth via mobile phones. In intervention group B, participating women will receive encouragement from a community-appointed volunteer to complete vaccinations recommended as well as a small cash reward for completing the recommended vaccinations. An estimated total of 200 women in the 10 treatment villages will receive one of the two study-initiated program interventions. No volunteer will be appointed to register births in the 5 control-arm villages and no woman in the 5 control-arm villages will be actively enrolled nor receive a pro-active program intervention during the intervention phase.

After the intervention phase is complete, an endline population-based household survey will be conducted in the 15 study villages to evaluate the effect of the intervention programs. The survey will enroll all consenting woman who have delivered a live-born baby in the last 12 months and reside in one of the 15 communities in the three study arms (10 intervention communities and 5 control communities). Based on a crude birth rate of 40 and an average village size of 100-1500 people, we estimate enrolling approximately 600-750 women in the endline survey. The endline survey will be used to compare the coverage of recommended early newborn vaccinations, and the proportion of births accurately and completely registered in each arm.

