### **Sample Size Calculation**

According to the latest Demographic and Health Survey from Ghana, about 50% of children in the Northern region receive both Bacillus Calmette–Guérin (BCG) and Polio vaccines within the first 30 days after delivery. We hypothesize that this proportion can be increased to 80% with either intervention

(reminder-only and incentives). Assuming 20 children in each cluster, and an intra-class correlation coefficient ( $\rho$ ) of 0.05, a sample size of 100 children is required in each active treatment arm (reminder-only and incentives) and in the control communities for comparison, to achieve power 0.9 at alpha 0.05. With a crude birth rate of 40, we expect 20 births in each community within six months of baseline for the average village with a population of 1000, which means that the targeted sample size for the active treatment program (100 per active treatment arm) should be achieved in less than six months.

The endline survey will be conducted in all communities in the three arms and will attempt to enroll all women who delivered a newborn in the previous 12 months. This will additionally allow us to compare outcomes of interest across treatment groups and in the pre- initiation and study intervention periods. We anticipate this will include approximately twice the number of births expected in the 6-month intervention period (600). To account for woman who may have been missed during the intervention period, refused to participate, or moved into the community after initiation, we propose a maximum of 750 woman for the endline survey.

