### **Study Duration and Follow-Up**

The two interventions will be implemented for six months in 10 pre-selected villages. During the six-month intervention period community volunteers will be engaged in recording all births in the catchment areas of the study communities.

The duration of participation for enrolled participants in each of the intervention arms will be approximately two weeks (soon after birth through two weeks of newborn life), with possible limited follow-up through 30 days of newborn life at the latest.

**Reminder arm (Intervention Group A):** Enrolled mothers will receive up to four voice or text messages to remind them of the importance and recommended timing of newborn vaccinations, starting from soon after birth and continuing through the first 10 days of newborn life (at approximately birth, 3, 7 and 10 days of life as appropriate). All contact with mothers will be completed by 30 days of newborn life at the latest.

**Incentive arm (Intervention Group B):** Enrolled mothers will receive contact and encouragement from community volunteers to complete newborn vaccinations, and volunteers will contact women to attempt to document vaccination status starting from soon after birth and continuing through the first 10 days of newborn life, with possible follow-up for encouragement and verification. All contact with mothers will be completed by 30 days of newborn life at the latest.

After the intervention period ends in both active treatment arms (30 days after the enrollment of the last participant in each of the 2 active intervention arms), an endline survey will be conducted in all 15 communities (10 intervention arm communities and 5 control arm communities).

**Endline survey:** During the endline survey period all households in the communities will be visited by a household surveyor over an estimated two-month period. Each interview is expected to take approximately 10-15 minutes.

No further contact with subjects in any of the three arms will be conducted after the completion of the endline survey.

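### The protocol does not limit the endline arm comparison, or the birth-registration denominator, to births within the six-month intervention period

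*Protocol*

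**What the plan says.** The Study Design Overview gives the endline household survey the task of evaluating the programmes: "The endline survey will be used to compare the coverage of recommended early newborn vaccinations" and the proportion of births registered, by arm. Its population is set in the same section: "The survey will enroll all consenting woman who have delivered a live-born baby in the last 12 months" and live in one of the 15 villages. The Endline Survey section repeats the 12-month eligibility. Nobody is enrolled in control villages during the intervention, so the survey is the only source of control data.

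The Study Duration and Follow-Up section runs both interventions for six months. It starts the survey 30 days after the last enrolment and adds that "all households in the communities will be visited by a household surveyor over an estimated two-month period". Volunteers are paid to report births during the same six months.

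The Primary and Secondary Outcomes section defines the primary outcome as BCG plus at least one polio dose within 28 days of delivery. The secondary outcome is the share of births found at endline that volunteers had reported. Neither definition has a birth-date limit. The Data Management and Statistical Analysis section gives a logistic GEE model and names no birth cohort or period term.

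The Sample Size Calculation section counts 20 births per village in six months. It expects the 12-month survey to hold about 600 births, twice the six-month number, and says that this additionally permits comparisons across arms and between the pre-initiation and intervention periods.

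**The concern.** The survey reaches back twice as far as the interventions lasted. A child born before the programme began, or after it ended, could not have been affected by it in the way the hypotheses intend. If such births enter the treated arms, the estimated effect moves toward zero. The protocol presents this as a pilot meant to inform estimates of potential impact, so a diluted estimate would mislead the planning of any larger study.

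Three related problems follow from the same wording:

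- The registration outcome has a denominator of all births found at endline, but its numerator can only come from the six months in which volunteers were reporting.
- The lookback moves with the interview date, so the mix of earlier, exposed and later births changes over the two-month survey.
- The eligibility rule admits infants under 28 days old, whose primary outcome may not yet be determined.

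In an open-label trial, leaving the set of births unspecified also leaves room for the choice to be made after coverage is known.

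**Working it through.** **Inputs.** From the Sample Size Calculation section:

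- Control coverage: "about 50% of children in the Northern region receive both" vaccines within 30 days (the outcome itself uses 28 days).
- Target: "We hypothesize that this proportion can be increased to 80% with either intervention".
- Clusters: "Assuming 20 children in each cluster", with ICC 0.05 and 100 children per arm.
- Error rates: "to achieve power 0.9 at alpha 0.05". Sidedness is not stated; two-sided is assumed here.
- Crude birth rate 40 per 1000 and an average village of 1000.

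From the Study Design Overview: 5 villages per arm and a 12-month lookback. From Study Duration and Follow-Up: six months of intervention, a survey start 30 days after the last enrolment, and about two months of survey.

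**1. The plan's own figure.** Two proportions, 0.50 vs 0.80, two-sided 0.05, power 0.90, no continuity correction: 52 per arm. Design effect 1 + (20 − 1) × 0.05 = 1.95. So 52 × 1.95 = 101.4, against 100 stated. At exactly 100 per arm the power is 0.902. The figure reproduces, and 5 villages × 20 births = 100 shows that it rests on six months of births.

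**2. The survey sample.** 15 villages × 1000 × 40/1000 = 600 births in 12 months, or 40 per village and 200 per arm. Six months give 300, or 100 per arm.

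**3. Make-up of the lookback.** Let s be the survey day. Later births cover 30 + s days, intervention births 183 days, and earlier births 365 − 183 − (30 + s) days.

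| Survey day | Before | During | After |
|---|---|---|---|
| 0 | 42% | 50% | 8% |
| 30 | 33% | 50% | 16% |
| 60 | 25% | 50% | 25% |

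About half of the births lie outside the intervention period on any interview date.

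**4. Contrast if all 12-month births are used.** Treated-arm coverage is 0.5 × 0.80 + 0.5 × 0.50 = 0.65. The difference is 15 points instead of 30.

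**5. Power for that contrast.** Design effect 1 + (40 − 1) × 0.05 = 2.95.

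- Unpooled variance: 0.25 + 0.2275 = 0.4775. SE = √(0.4775 × 2.95/200) = 0.0839. Ratio 0.15/0.0839 = 1.787. Power = Φ(1.787 − 1.960) = 0.43.
- Null variance pooled, the formula that gave 0.902 in step 1: power 0.42.
- For reference, the unpooled formula gives the planned design SE = √(0.41 × 1.95/100) = 0.0894, ratio 3.355, power 0.92.
- With a t reference on 8 df, the planned design has power 0.84 and the diluted one 0.35.

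Like for like, dilution takes power from 0.90 to 0.42, from 0.92 to 0.43, or from 0.84 to 0.35. At 40 births per village, 90% power for 50% vs 65% would need 227 × 2.95 ≈ 670 children per arm.

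**6. Registration outcome.** Volunteers can report at most 6 of the 12 months of births in the denominator, so the ceiling is 6/12 = 50%.

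**7. Open outcome windows.** 28/365 = 7.7% of lookback births are under 28 days old at interview. As the survey starts 30 days after the last enrolment, these are essentially births after the programme.

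**The case against.** A reader might infer that the protocol pools all 12-month births and that the trial will therefore report half the true effect. The documents do not support that as a statement of fact. The 12-month rule is survey eligibility, not a declared analysis set. The Sample Size Calculation section sizes the trial on six-month births, recognises that the survey holds about twice that number, and foresees distinguishing the two periods. An intervention-period comparison with earlier births as a reference is a natural reading of it. Two further inferences also lack a basis: no section says that infants under 28 days count as failures, and none describes an order of survey that would tie the period mix to arm.

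It can also be argued that birth-date limits are ordinary analysis-plan detail, and that an SAP, which is not shown, may supply them. For a missing period term alone, that would be fair.

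What the objection does not remove is the text the protocol does fix. The only population it names for the arm comparison is the 12-month sample, while the sizing uses half of it, and the foreseen period comparison is not identified as primary. It is also silent on births after the programme. The secondary outcome's denominator is written into the protocol and does not match the reporting period.

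**Conclusion.** The point holds as an unresolved definition, not as a proven pooling of births. The protocol leaves open which births enter the primary comparison, and its literal wording admits about twice as many as the design assumed, half of them unexposed. On that reading the expected difference falls from 30 to 15 points and normal-theory power from about 0.90 to about 0.42 to 0.43. These figures assume births spread evenly over the year, the full hypothesised effect in births during the intervention, no effect in the others, an unchanged ICC of 0.05 with 40 births per village, and a two-sided test.

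The registration outcome is the more exposed of the two. Its ceiling of about 50% follows directly from the stated denominator, and H3 could not be judged fairly against it.

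**What to change.** Add to the outcomes and analysis sections:

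- The primary comparison uses all births identified at endline with a date of birth within the six-month intervention period, whether or not the mother was enrolled. The same calendar dates apply in control villages.
- Only infants at least 28 days old at interview are included. This covers unenrolled births that fall after the last enrolment, which the 30-day gap does not guarantee to be past day 28.
- The registration outcome in the intervention villages uses the same birth-date limits for its denominator.
- Pre-initiation births serve only as baseline or for the period-by-arm comparison. Births after the programme are left out of the primary analysis.

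The 12-month survey eligibility can stay. Six months of intervention, 30 days and a two-month survey come to about nine months, so the lookback still captures every intervention-period birth. No criterion on residence at delivery is needed.

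The cost is a few sentences. Date of birth is already collected in the survey. The primary analysis uses about 300 rather than 600 births, which is what the power calculation assumes.

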## Methodology

To assess the feasibility and effectiveness of the proposed early vaccination support platforms, we will conduct a pilot study in 15 rural communities in Northern Ghana. The 15 communities will be divided into 3 groups: 1) a **reminder-only intervention group** (Intervention Group A, 5 communities), 2) an **incentivized reward group** (Intervention Group B, 5 communities); and a **control group** (5 communities). Approximately 200 mothers (100 per treatment arm) will be enrolled in intervention programs across the two treatment groups.

### *Community Volunteer Appointment and Birth Registration*

In all of the 10 intervention arm communities, we will implement sensitization meetings at the beginning of the study to explain the purpose and objective of the proposed work. We will then ask the community to appoint a local birth registration volunteer. Minimum qualifications for the local birth registration volunteer include the following: female; owns and has daily access to a smart phone with camera capability and the knowledge and ability to take photos and send SMS messages; is a member of the local community and in good standing with the community; speaks the local language fluently and has at least a minimum working knowledge of English and Dagbani; can read and write (local language fluency and working knowledge of English).

Candidate volunteers will be informed of the expectations of participating in the project, the project duration (6 months), the expected time commitment per week (approximately one hour per week in the incentive program areas and 30 minutes per week in the reminder-only program areas). They will then be invited to accept or decline the appointment as a birth registration volunteer. Birth registration volunteers who accept the appointment will undergo a standardized training to further inform them of the procedures and expectations of their role, and to provide practical advice on successfully engaging in their role.

Community volunteers will be expected to document and report all births in their communities to a central phone hotline which will be managed by study personnel. To motivate volunteers to report all births in their communities, and to compensate them for their efforts, they will be given a 2 cedis reward (USD 0.50) for each birth reported during the active study duration (6 months).

**Intervention arm A (“reminders only”)** focuses on automated voice and text messages sent to mothers. In this treatment arm, community volunteers will register all births in the community as described above.

**All women who live in this community and have given birth to a live-born newborn in the previous week are eligible for enrollment.** As soon as possible after each birth, volunteers will contact the mother to briefly introduce the study and ask if they are interested in receiving vaccination-related information via voice messages and SMS on their phones. If the woman is interested, volunteers will describe the study purpose and procedures in more detail, answer any questions the woman has about participation, and guide the woman through the informed consent process. If mothers sign the written informed consent document (see *Informed Consent Reminder Intervention*), volunteers will ask the woman to provide a phone number of their choice at which they would like to be contacted to receive vaccine-related information and reminders. The volunteers will send the phone number provided by enrolled woman, together with a copy of the signed consent form, to a central study system.

An initial (automated) voice call will be made to all enrolled mothers to congratulate the mother on the birth and to highlight the importance of early vaccinations for their newborns. The message will also recommend that the mother take the newborn to get the BCG and Polio0 vaccine as soon as possible after birth if the newborn has not yet received these vaccines, ideally within two weeks after birth (as per Ghana national recommendations on immunization schedule). Additional reminder text messages will be sent to the phone number provided to the mother at 3 days, 7 days and 10 days of newborn life (as appropriate), reminding the woman to complete these vaccinations for her child. The text reminders will be short messages that reiterate the importance of early newborn vaccination for BCG and polio and will encourage woman to seek these vaccines for their newborns within the first two weeks of life if the newborn has not yet received them.

All mobile communications will include a note stating that if the woman prefers to stop receiving additional reminders or information she can flash (briefly call) the study phone line and they will call her back at no cost to her, so that she can request to stop receiving messages. She will also be informed that she can send a simple “STOP” text message to the same mobile number which sent the reminder (or voice message). Messages will continue to be sent to the woman through approximately the first two weeks of newborn life. The duration of follow-up with enrolled woman will be two weeks after enrollment in the study. Community birth registration volunteers will not contact enrolled participants in this arm (or women who meet eligibility criteria but chose not to be enrolled) after the completion of the birth registration and informed consent procedure is completed.

Enrolled participants in this arm will not receive any monetary compensation, incentive or reward for participation.

**Intervention arm B (“incentives”)** relies more directly on community volunteers. In the incentives arm, community volunteers will similarly register all births in their community during the intervention phase. The volunteers will receive a 2 cedis phone credit reward for each birth registered in their community.

**All women who reside in the community and have given birth to a live-born newborn in the previous week are eligible for enrollment.** Volunteers will contact mothers as soon as possible after birth and will introduce the study purpose and procedures and ask if the woman may be interested in participating. If the woman is interested the volunteer will guide them through the informed consent process and will describe in more detail the study purpose and procedures and answer any questions the woman may have about participation. If the woman then agrees to participate and signs the written informed consent document they will be enrolled in the study (see *Informed Consent Incentives*). No incentive will be provided to the volunteer or to the mother on the grounds of study enrollment.

Mothers will be informed that the program aims at improving early vaccination coverage for newborns, and that they will receive a small reward (2 cedis) if their baby receives both the BCG and the first dose of polio vaccination within the first two weeks of newborn life.

Mothers will be informed that if they decide to participate, the volunteer may contact them to encourage them to vaccinate their newborn and to document the vaccination if the woman reports that one or both vaccinations have been completed. Volunteers may contact enrolled woman via phone voice message, call, text or in person at the household to provide information about early vaccination and to encourage the woman to vaccinate her child.

If the woman reports to the volunteer that she has completed the vaccinations, the volunteer will document vaccination status and dates of completion, take a photo of the vaccination card and/or record the date and location that each of the vaccinations was received. The volunteer will not conduct any further follow-up with women who report completion of both early vaccines.

Volunteers will report the successful completion of both vaccinations along with the photo and/or location and date to the central study hotline for verification. As proof of completed vaccination, the volunteer will either need to submit a picture of the vaccination card, or provide the date and location of each vaccination to the project phone line for verification. If both vaccines were successfully completed within the first two weeks of newborn life, the mothers and community volunteers will each receive a small reward of 2 cedis (0.50 UDS).

Mothers in the incentives arm will not receive automated voice messages or automated SMS text reminders for vaccination.

The study hotline and management of the mobile system for sending automated voice messages and SMS texts to enrolled participants will be managed by the local implementing partner, Innovations for Poverty Action Ghana (IPA Ghana). The appointment of community volunteers in both treatment arms, management of informed consent documents and supervision of the list of enrolled participants, verification and distribution of incentives to volunteers for registering births and vaccination completion for women in the incentives arm will also be managed by IPA Ghana.

